#### The national implementation

The national implementation will be driven by clinicians who have attended the course and are trained in GLA:D Back. Therefore, the first step was to generate awareness of the development of GLA:D Back in professional journals, at seminars and meetings, and by mentioning the new initiative at the GLA:D Knee/Hip courses. Then, in August 2017, nine clinics (31 clinicians) participated in piloting the GLA:D Back program and took their own initiatives to promote their participation via websites, social media and contact with GPs.

In February 2018, when course registration opened for all interested chiropractors and physiotherapists, the Danish Physiotherapy Association and the Danish Chiropractors’ Associations and some physiotherapy special interest groups were asked to advertise the program to their members. The GLA:D Back website, and an invitation to register, were also promoted by the research team on Facebook, LinkedIn and Twitter and to clinicians who use the GLA:D register for knee/hip patients when they logged on to the registry (Table 2). Course participation is at a cost of approximately €550 (2018).

**Table 2 Tab2:** Promotion activities and pre-defined minimum standards for the planned activities and for reach

Planned promotion activity	Interval	Minimum standard
Article on the Danish Physiotherapists’ web site	Completed 2017	NA
Poster presentation Danish Chiropractors’ Association meeting	Completed 2017	NA
Series of three letters on standardised care in a magazine for members of Danish Chiropractors’ Association	Completed 2017	NA
The Danish Chiropractic Association (DCA) informs members that course registration is open	Once before registration opens	One newsletter e-mailed to members of the DCA News posted on the DCA’s website
The Danish Physiotherapy Association informs members that course registration is open	Once before registration opens	One newsletter e-mailed to members of the Association News posted on the Association’s website
Information about the GLA:D Back courses at websites of physiotherapy special interest groups - Musculoskeletal physiotherapy - Sports physiotherapy - Physiotherapists in private practice - Physiotherapists without a contract with the board of wages and fees	Once before first course registration closes	One of the listed groups posts the information
Direct e-mail to the five regions’ private practice consultants from chiropractic, physiotherapy and general practice	Once when information about opening the registration is known	Mail send before registration opens
Information to clinicians who deliver GLA:D for knee/hip patients on the front page of the knee/hip clinical registry	When registration is open	Information posted one time before opening
Promotion of GLA:D Back via social media (Twitter, Facebook, ResearchGate, LinkedIn)	When GLA:D Back related external activities (courses, talks) and publications occur	One posting per month during 2018
Workshop at the yearly seminar for general practitioners “Lægedage”	November 2018 + November 2019	One workshop accepted
Clinicians who participated in the course and wanted to deliver the intervention listed at the GLA:D Back website	After courses are conducted for a region	Updated within 2 weeks of the last course for a region
Target	Group definition	Minimum standard
Number of clinicians educated in 2018	The Capital Region of Denmark	60
	Region Zealand	60
	Region of Southern Denmark	60
	Central Denmark Region	60
	The North Denmark Region	60
	Total	300
Years of clinical experience (min. proportion)	0–5	10%
	> 15	10%
Sex	Proportion males	Min 33% Max 66%
Work place and role (min. proportion)	Municipality	5%
	Private clinics	60%
	Clinic owner	5%
	Employed clinician	50%
Profession (minimum proportion)	Physiotherapist	70%
	Chiropractor	10%

Clinicians who participate in the course and decide to deliver GLA:D Back at their clinic are listed as certified clinicians on the GLA:D Back website (http://gladryg.sdu.dk/). Because GLA:D is a registered trademark, only clinicians trained at SDU can use the brand, and sustained certification comes with the requirement to enter all appropriate patient information into the clinical registry. Updates and re-certification are planned for the future.

To support the implementation after the course, clinicians are given access to detailed patient educational materials, exercise programs, and written suggestions of language that can be used in the supervision of exercises after the course. They also are given GLA:D Back logo t-shirts and posters for the clinic with key messages from the patient education and an overview of the exercises [30]. To assist a uniform promotion of the program, clinicians get information leaflets directed at patients and at GPs that can be used with their individual clinic names and logos.

There are no strict patient inclusion criteria, and the decision to enrol a patient in GLA:D Back is at the discretion of the clinician in a dialogue with the patient, when clinicians judge that the patient would benefit from improved self-management skills. Patients can be enrolled at the first visit or later depending on whether individual treatment sessions are deemed necessary prior to starting GLA:D Back. When patients begin the program their contact information is entered in the clinical registry, which in turn activates links to patient questionnaires that are sent automatically on the day of registration and again after 3, 6 and 12 months. Clinicians enter results of physical tests and patients’ individual goals in the registry before patients start the GLA:D Back intervention and when the program ends. The price and out-of-pocket expenses for the GLA:D Back intervention can vary between clinics and types of insurance.

Consultants for physiotherapy, chiropractic, and family medicine working with primary care in the five administrative regions were invited to an information meeting about GLA:D Back before course registration was opened (January 2018). Family physicians will be informed through professional journals and seminars.

### Effectiveness and process evaluations

#### Data collection

Data sources will include: 1) data obtained from clinicians when they register for a GLA:D Back course, 2) clinician-completed surveys before and directly after the course and after 5- months, 3) observations of patient education and exercise group sessions in selected clinics, 4) patient physical tests at baseline and at the end of treatment, 5) patient-completed surveys at baseline, 3-months, 6-months and 12-months, 6) patient interviews, and 7) information from Danish registries (Fig. 5). Patient and clinician data are collected electronically using the REDCap software (Vanderbilt University) provided and supported by the Odense Patient data Explorative Network (OPEN) [41].

**Fig. 5 Fig5:**
[figure not shown]
Study timeline. * Clinician data collected before and after the course

#### Evaluation of the clinical intervention

The clinical intervention will be evaluated based on data about the patients who enrol in the GLA:D Back program, i.e. those patients who are registered in the GLA:D Back registry.

Due to the lack of a control group we will compare mean changes in these patients with those observed in the intervention groups of trials that have demonstrated positive effects of patient education and exercise therapy. We will look for trials with little risk of bias that included patient populations comparable with those enrolled in GLA:D Back.

Health care utilisation and sick leave will be investigated using national registry data to compare individual patterns of health care utilisation (primary care visits, hospital visits due to LBP, imaging for LBP, prescriptions for pain medication) and sick leave from 1 year before participation in GLA:D Back to 1 year after participation (Fig. 5).

Clinicians’ beliefs about back pain and confidence in managing patients with LBP (described below) and their baseline characteristics will be investigated as potential predictors of patient outcomes. Potential mechanisms of change in patients will be investigated by testing the mediating pathways outlined in the theoretical model (Fig. 3). We will specifically test the extent to which improved illness beliefs, increased perceived ability to perform exercises, and improvements on physical tests may explain a reduction in fear avoidance, improvement in expectations and increased self-assessed physical capacity during the 3 months after inclusion and during the following 3 months (3- to 6-months follow up). We will then test to what extent reduced fear avoidance beliefs, improved expectations and increased physical capacity during the initial 3 months relate to an increase in self-efficacy during the same period and to improved self-efficacy after 6 and 12 months. Next, we will investigate the relationship between increased self-efficacy and outcomes of self-management success, and whether self-efficacy is a mediator between beliefs and performance and success in self-management. Lastly, we will test to what extent improvements in disability, quality of life and pain after 6 months predict health care utilisation and sick leave after 12 months, to what extent improved self-efficacy influences these outcomes, and if this is fully or partly explained by improvements in self-management.

Patients’ perceptions related to developing pain self-efficacy and ability to self-manage will be explored using individual interviews that address back beliefs, perceived ability to manage LBP, and what aspects of the LBP experience need to change during and after participation for patients to consider the intervention beneficial.

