In summary, there is evidence that implementation interventions can change healthcare practitioner behaviours and potentially improve patient outcomes [12]. However, we could not find examples of studies documenting outcomes of nationwide implementation of back pain treatments, nor did we find investigations of whether implementation of recommended care can be achieved by making training generally available to back pain clinicians. Finally, there is a need for understanding how back pain treatments work in a general clinical context.

This protocol describes a hybrid effectiveness-implementation type 3 study [29], which will evaluate the national implementation of a standardised care package for people with back pain, GLA:D Back [30]. GLA:D Back will expand an existing program ‘Good Life with OsteoArthritis in Denmark’ for patients with knee or hip pain to people with back pain [31]. It aims to improve self-management in people with persistent or recurrent back pain by translating recommendations from clinical guidelines into an intervention that consists of group-based patient education and supervised exercises with data from patients enrolled in GLA:D Back included in a clinical registry that monitors patient profiles and outcomes. The main activity for implementation consists of a course for physiotherapists and chiropractors in delivering GLA:D Back and access to materials needed for the delivery of this intervention. The mode of implementation was tested in a feasibility study with physiotherapists and chiropractors from nine clinics that all managed to implement the intervention following the course. These pilot clinics enrolled 89 patients in the GLA:D Back programme and 161 in two comparison groups as part of the feasibility testing. A mixed methods evaluation showed good promise for adoption of the clinical intervention after clinicians’ course participation, for the data collection and for positive outcomes with the GLA:D Back intervention [32].

This protocol describes the methods for evaluation of the initial roll-out of GLA:D Back. This includes evaluating the clinical intervention targeted at patients, the educational intervention targeted at clinicians, and the national implementation.

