The study objectives for the evaluation of the clinical intervention are:To describe changes in patient outcomes after participation in GLA:D Back and evaluate if these are of a magnitude comparable with those observed in RCTs on combined patient education and exercise interventions for persistent and recurrent back pain,To determine to what extent patterns of health care utilisation and sick leave change in individuals from one year before participation in GLA:D Back to one year after,To determine if patient outcomes are associated with clinicians’ treatment orientation and confidence,To identify subgroups of patients who do not benefit sufficiently from the GLA:D Back clinical intervention, andTo investigate potential mechanisms of change in patient outcomes.

With respect to within subject changes we hypothesise that the clinical intervention is as effective as previously observed changes in RCTs on similar interventions.

The study objectives for the evaluation of the clinician educational intervention are:To monitor outcomes of learning activities and adapt the delivery of the clinician course accordingly,To determine if there is a change in treatment orientation from a biomedical to a more behavioural orientation and an increase in clinicians’ confidence in managing people with back pain following the GLA:D Back course,To identify clinician factors related to treatment orientation and confidence in managing back pain, andTo determine if treatment orientation and clinicians’ confidence are associated with clinical behaviours.

We hypothesize that the educational intervention is effective in preparing the clinicians to deliver the clinical intervention as intended.

The study objectives for the evaluation of the national implementation are:To monitor the promotion of GLA:D Back courses and adapt the promotion strategy when prespecified criteria are not met,To describe the penetration, adoption, and fidelity of GLA:D Back including the degree of uniformity across clinicians, clinics, and regions,To identify individual and organisational determinants of adoption and fidelity, andTo evaluate the effects of the implementation on referrals to imaging and secondary care for back pain, opioid prescription, and sick leave rates at the national level.

We hypothesize that in the long run the implementation will imply reductions in referrals to imaging and secondary care and in opioid prescriptions for back pain at the national level.

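### A benchmark built only from intervention arms of positive trials cannot support a claim of equal effectiveness, and the positive-result filter tends to set the bar too high

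*Protocol article*

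**What the plan says.** The first objective for the clinical intervention (protocol article, Background) is to describe patient changes and "evaluate if these are of a magnitude comparable with those observed in RCTs on combined patient education and exercise interventions". It covers randomised trials in general, with no condition on their results. The hypothesis below it reads: "With respect to within subject changes we hypothesise that the clinical intervention is as effective as previously observed changes in RCTs on similar interventions".

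The section Evaluation of the clinical intervention gives the method. It starts from the absence of a concurrent comparison ("Due to the lack of a control group") and sets the rule that "we will compare mean changes in these patients with those observed in the intervention groups of trials that have demonstrated positive effects". It adds two further criteria: "We will look for trials with little risk of bias that included patient populations comparable with those enrolled in GLA:D Back". That section gives no role to the control groups of the benchmark trials.

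Three other places bear on this. The Discussion acknowledges that the effect of the clinical intervention is studied only through a pre-post comparison. The section on the national implementation sets no strict inclusion criteria and leaves enrolment to the clinician in dialogue with the patient. Statistical analyses and reporting promises a detailed analysis plan for each subproject.

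**The concern.** The patient-level hypothesis rests on this benchmark, and the benchmark is drawn from one side of each trial and from one kind of trial.

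- **One side.** The mean change in an intervention arm is not a treatment effect. It also contains natural course, regression to the mean and non-specific response. These need not be the same in discretionary registry enrolment as in a trial population. A similar change could therefore come from a programme that works equally well, or from one that works less well in patients who would have improved more anyway.
- **One kind.** Keeping only trials with positive results selects on the outcome. Such trials tend to have intervention arms with favourable chance error, so the bar tends to sit above the true mean.

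The first fault could yield an effectiveness conclusion that the data cannot carry. The second could make an adequate programme look deficient. Both are rules stated in the text, not details left open for a later plan.

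**Working it through.** **The plan's own figure.** Sample size gives 1500 patients, a variance inflation factor up to 5, effect size 0.2 and 90% power. The effective sample is 1500/5 = 300. With two-sided alpha 0.05 (assumed; none is stated), power = Φ(0.2·√300 − 1.96) = Φ(1.504) = 93.4%. The stated 90% is thus slightly conservative and not a problem here. This calculation tests change against zero. It says nothing about comparison with a benchmark. At the same inflation factor, the 95% confidence interval for the mean change is ±1.96/√300 = ±0.11 SD.

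All inputs below, apart from the effective 300, are assumptions. The documents give no trial sizes, trial effects or comparability margin. Changes are in SD units.

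**(a) How much of an arm's change is not treatment effect?** Share = u/(u + d), where u is the change that would occur without the treatment effect and d is the true effect.

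| u | d = 0.2 | d = 0.3 | d = 0.5 |
|---|---|---|---|
| 0.2 | 50% | 40% | 29% |
| 0.4 | 67% | 57% | 44% |
| 0.6 | 75% | 67% | 55% |

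**Can an ineffective programme match?** Assume a margin of 0.2, an effective 300 patients on each side and a trial effect of 0.3. Let o be the extra non-treatment change in registry patients. The standard error is √(1/300 + 1/300) = 0.0816. The chance that a programme with zero effect is declared comparable is Φ((0.2 − (0.3 − o))/0.0816 − 1.96):

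- o = 0: 0.1%
- o = 0.1: 2.5%
- o = 0.2: 23%
- o = 0.3: 69%

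So a match is misleading only if non-treatment change differs between registry and trials. An intervention-arm benchmark gives no means of judging that.

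**(b) What does the positive-result filter do?** For a two-arm trial with n per arm, let δ = d/√(2/n). Keeping only trials with Z > 1.96 raises the expected intervention-arm change by ½·(E[Z | Z > 1.96] − δ)·√(2/n). For n = 50 and d = 0.2, √(2/50) = 0.2 and δ = 1.0. The excess in Z is φ(0.96)/(1 − Φ(0.96)) = 1.49, and ½ × 1.49 × 0.2 = 0.149. Simulation of 400,000 trials per setting gives:

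| n per arm | d = 0.2 | d = 0.3 | d = 0.5 |
|---|---|---|---|
| 50 | 0.149 | 0.111 | 0.049 |
| 100 | 0.083 | 0.049 | 0.009 |
| 200 | 0.039 | 0.014 | 0.000 |

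**Direction of (b).** Suppose the true changes are equal, with the same margin and sample sizes. The chance of declaring comparability is Φ((0.2 − inflation)/0.0816 − 1.96): 69% with no inflation, 45% at 0.05, 23% at 0.10 and 9% at 0.15. The filter works against the hypothesis.

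**The case against.** The case for the plan is substantial. The study is a type 3 hybrid, which by the article's own definition tests the implementation strategy while observing outcomes of the clinical intervention. Its authors treat the effect as established in trials and ask whether practice reaches a similar change. The hypothesis is worded for within-subject changes, and the pre-post limit is disclosed. The positive-result filter also has a rationale: it ensures that the benchmark trials' control arms did worse, and admitting null trials brings in intervention arms that did not beat their controls.

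Much of this stands, and it lowers the severity. It does not remove the fault. A positive result shows that a difference existed in the trial. It does not show how much of the arm's change was difference, nor that the remainder is the same in registry patients. Showing both arms answers the worry about null trials, because the reader then sees which arms outperformed their controls. The qualifier about within-subject change still sits in a sentence claiming equal effectiveness.

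Three stronger readings are tempting but not supported:

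- A reader might infer that an inflated benchmark is what makes a match worthless. The direction is the reverse: a higher bar makes a match harder. A match is uninformative because of the missing control arms.
- A reader might infer from "included patient populations comparable with those enrolled in GLA:D Back" that matching inflates the benchmark, or that trials will be picked after outcomes are known. Matching populations is sound practice, and nothing says when trials are chosen. The subproject analysis plans may fix the list.
- A reader might look to the pilot's "161 in two comparison groups as part of the feasibility testing" as a ready control. The article does not describe those patients or their follow-up, so they cannot be put forward as a reference.

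**Conclusion.** The point holds as two separate faults, at the level of should-fix.

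(a) Intervention-arm change without control-arm change cannot support an effectiveness claim. Under the assumed ranges, 29% to 75% of such a change is not treatment effect. The exact share is unknown from the documents, but the argument needs only that it is not zero and may differ between registry and trials.

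(b) Selecting on positive results departs from the first objective and probably raises the benchmark. The size is about 0 to 0.15 SD for 50 to 200 patients per arm and true effects of 0.2 to 0.5 SD. It is close to zero for large trials or strong effects, and at its largest exceeds the ±0.11 SD half-width above. The low-risk-of-bias criterion may limit it. Its bias is towards a false shortfall.

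The disclosed limits soften the problem without curing it.

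**What to change.** In Evaluation of the clinical intervention, drop the condition on trial results. Take all eligible low-risk-of-bias trials of combined patient education and exercise in comparable populations with persistent or recurrent low back pain. Report the GLA:D Back mean change with its cluster-adjusted confidence interval beside both the intervention-arm and the control-arm changes, stating what each control arm received, since an active control is not an untreated course.

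In the Background hypothesis, replace the equal-effectiveness wording with: change of similar size to that in trial intervention arms.

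The design and patient data collection are unchanged. The cost is slightly more extraction from publications already under review, and a benchmark that may be more heterogeneous. Control-arm figures will not turn this into a controlled comparison. They only let the reader see how much change the trials recorded without the intervention.

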#### Evaluation of the clinician educational intervention

All clinicians participating in a course will be included in this evaluation. The course content and delivery will be evaluated via observations by an expert in medical education to confirm that the planned learning activities are delivered. Outcomes of learning activities (Table 1) will be compared between courses and any trends in change over time described.

Evaluations of clinician-level outcomes will be investigated in an observational longitudinal design with clinician-reported data collected before the clinician training course, immediately after the course and 5 months later, and with patient-reported information on delivery collected at their three-months follow up. Changes over time in treatment orientation and confidence in managing patients with LBP will be described, and potential relationships between clinician characteristics, treatment orientation and confidence will be determined.

